## 5.2 Exclusion Criteria

Subjects are excluded from the study if any of the following criteria apply:

1. Subject has prior anticancer or investigational drug treatment within the following windows:
  - a. Prior treatment with an inhibitor specific to KRASG12C mutation, such as AMG 510, MRTX849, LY3499446, JDQ443 and GDC-6036 (for subjects received previous treatment of KRASG12C inhibitors, the subjects are acceptable to participate in [REDACTED] [REDACTED] Prior treatment with EGFR inhibitors (for [REDACTED] [REDACTED] Phase 2 Arm F subjects only).
  - b. Any anticancer therapy (including chemotherapy, targeted therapy, immune therapy, etc.) or any other investigational drug therapy less than 14 days or 3 half-lives (whichever is shorter) prior to first dose of study intervention.
2. Subject with unstable or progressive central nervous system (CNS) metastases and/or carcinomatous meningitis. Subjects with history of brain metastases are allowed, if they are clinically stable. [REDACTED]  
[REDACTED]  
[REDACTED]  
[REDACTED]  
[REDACTED]  
[REDACTED]  
[REDACTED]
3. Subjects with clinically significant cardiovascular disease, including:

- Subject with acute myocardial infarction, severe/unstable angina; or with cardiac insufficiency of New York Heart Association Functional Classification Grade 2 or above;
  - Subject has corrected QT interval using Fridericia's formula (QTcF) prolongation at rest, where the mean QTc interval is  $> 470$  msec based on triplicate measurements of electrocardiogram (ECG);
  - History or current evidence of serious uncontrolled ventricular arrhythmias requiring drug therapy;
  - Left ventricular ejection fraction (LVEF)  $< 50\%$  (for [REDACTED] [REDACTED] [REDACTED] Arm F subject only);
  - Congenital long QT syndrome, or any known history of torsade de pointes (TdP), or family history of unexplained sudden death;
  - Clinically uncontrolled hypertension (after standard antihypertensive treatment, systolic blood pressure  $\geq 150$  mmHg and/or diastolic blood pressure  $\geq 100$  mmHg).
4. Subject has a history of (non-infectious) pneumonitis/interstitial lung disease that required steroids or has current pneumonitis/interstitial lung disease or any active systemic infection including but not limited to severe acute respiratory syndrome coronavirus 2 (SARS-CoV-2) infection.
5. For China and Taiwan region sites only [REDACTED]  
[REDACTED]
- Subject with human immunodeficiency virus (HIV) infection (positive HIV 1/2 antibody), hepatitis B infection (positive hepatitis B surface antigen), or hepatitis C infection (quantitative HCV RNA result greater than the lower limit of detection of the assay).
- [REDACTED]  
[REDACTED]
6. Subject has any history or evidence of substance abuse or medical, psychological or social conditions that may, in the opinion of the investigator, interfere with participation in the study or evaluation of the study results.
7. Subject has impaired gastrointestinal (GI) function or GI diseases that may significantly alter the absorption or metabolism of oral medications.
8. Other serious illness or medical conditions at the investigator's discretion, that may influence study results, including but not limited to serious infection, diabetes, cardiovascular and cerebrovascular accident (CVA) ( $< 6$  months before study entry) and lung disease.

9. Subject has unresolved toxicities from prior anticancer therapy, defined as toxicities (other than alopecia) not yet resolved to NCI CTCAE, v5.0, Grade  $\leq 1$  (Grade  $\leq 2$  for peripheral neuropathy).

[REDACTED]

10. Subject had major surgery within 4 weeks prior to study treatment administration or last dose of palliative radiation therapy within 2 weeks prior to study treatment administration.

- Subject must have recovered adequately from the surgery and/or any complications of the surgery prior to starting study treatment.
- Subject must have recovered from all radiation-related toxicities, not requiring corticosteroids, and with no occurrence of radiation pneumonitis. A 1-week washout is permitted for palliative radiation that lasted  $\leq 2$  weeks for non-CNS disease.

11. Subject has received radiation therapy  $>30$  Gy to the lung within 6 months of the first dose of study treatment

12. Subject with uncontrolled pleural effusion, pericardial effusion or ascites. A subject who is clinically stable following treatment for these conditions (including therapeutic thoraco- or paracentesis, indwelling catheters) is eligible.

13. Subject is currently receiving or planning to receive medications known to be substrate of CYP3A4 with a narrow therapeutic window, strong inducer or strong inhibitor of CYP3A4, with a known risk to prolong the QT interval or strong inhibitor of P-glycoprotein within 14 days or 5 half-lives of the drug or its major active metabolite, whichever is shorter, prior to study day 1 [REDACTED]

[REDACTED]

14. Subject has any other known primary malignancy that is progressing or has required active treatment within the past 3 years. Note: subjects with basal cell carcinoma of the skin, squamous cell carcinoma of the skin, or carcinoma in situ (e.g., breast carcinoma, cervical cancer in situ) that have undergone potentially curative therapy are not excluded.

15. Subject is pregnant or lactating.

16. [REDACTED]

- [REDACTED]  
[REDACTED]
- [REDACTED]  
[REDACTED]  
[REDACTED]
- [REDACTED]  
[REDACTED]
- [REDACTED]  
[REDACTED]  
[REDACTED]  
[REDACTED]  
[REDACTED]
- [REDACTED]  
[REDACTED]
- [REDACTED]  
[REDACTED]
- [REDACTED]
- [REDACTED]  
[REDACTED]  
[REDACTED]  
[REDACTED]

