7. Serum or urine pregnancy tests will be performed at Screening, Pre-Dose Day -1 and End of Treatment or Withdrawal as well as on Day 1 of every odd-numbered cycle (except Cycle 1). Subjects with a positive pregnancy test will be permanently discontinued from treatment with study intervention and will enter into a safety follow-up period.
8. ECOG performance status grade is available in [Appendix 1](#) of the protocol
9. KRASG12C mutation status must be documented for the purpose of the inclusion criteria using a blood or tumor tissue sample and can be from a previously conducted local laboratory test result up to 5 years prior to this study. The method used for the test should also be collected.
10. Vital signs include body temperature, pulse, respiratory rate and blood pressure. These should be done once pre-dose and once post-dose on dosing days, and once on non-dosing days (pre-and post-dose procedures in BID cohort will only be required for the first dose during the day). Both pre-dose and post-dose measurements can have 1-hour window.
11. Laboratory assessments include hematology, blood chemistry, urinalysis and coagulation. Weekly or more frequent tests may be given at the investigator's discretion:  
Hematology includes complete blood count including RBC, hemoglobin, hematocrit, WBC and differential (neutrophils, eosinophils, basophils, lymphocytes, monocytes and other cells) and platelet count. Blood chemistry includes total, direct and indirect bilirubin, ALT, AST, ALP, LDH, total protein, albumin, sodium, potassium, magnesium, chloride, calcium, phosphorus, BUN, creatinine, uric acid, glucose. Additional blood chemistry tests may be performed as clinically indicated (e.g., amylase, lipase, creatinine kinase, GGT). Urinalysis includes pH, specific gravity, protein, glucose, ketones, RBC, WBC, bilirubin. Additional analyses may be required as clinically indicated. Coagulation parameters should be determined throughout the study when clinically indicated or warfarin is to be administered, including aPTT and INR.

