## 2.5 Pharmacokinetics and ADME

Various experiments were performed to evaluate PK profiles of D-1553, including absorption studies in both beagle dogs and Sprague Dawley rats, distribution and excretion studies in Sprague Dawley rats, and metabolism studies in the hepatocytes of different species.

PK and absorption, distribution, metabolism and excretion (ADME) of D-1553 have been thoroughly characterized. [REDACTED]

[REDACTED] No sex-related differences in PK parameters were seen in rats, and no accumulation of D-1553 was observed in rats or dogs with dosing up to 7 days.

D-1553 was distributed to all tissues within 0.5 hours [REDACTED]  
[REDACTED]  
[REDACTED]  
[REDACTED]  
[REDACTED]  
[REDACTED]

Cytochrome 450 (CYP) phenotyping studies using human liver microsomes identified CYP3A as the major metabolic enzyme [REDACTED]  
[REDACTED]

No induction of CYP1A2 or 3A4 enzyme activity or gene expression was observed in hepatocytes.  
[REDACTED]  
[REDACTED]

D-1553 weakly inhibited CYP3A4 but had minimal/negligible effects on CYP1A2, CYP2B6, CYP2C8, CYP2C9, CYP2C19 and CYP2D6.  
[REDACTED]  
[REDACTED]

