- Disease relapse during treatment or within 6 months following adjuvant therapy will be considered advanced or metastatic disease;
  - Patients who have received 2 prior regimens (i.e. those entering the study in the 3rd line setting), must have received oxaliplatin unless it was contraindicated due to underlying conditions.
8. Subject has measurable disease according to RECIST, v1.1. For Phase 1 portion, subject with evaluable disease according to RECIST, v1.1 is also acceptable.
9. Subject in Phase 1 has an Eastern Cooperative Oncology Group (ECOG) performance status of Grade  $\leq 2$ , [REDACTED]. Subject in Phase 2 has an ECOG performance status of Grade 0 or 1.
10. Subject has adequate hematologic function, defined as:
- Platelet count  $\geq 100 \times 10^9/L$ ;
  - Hemoglobin level  $\geq 8.0$  g/dL. [REDACTED]
- [REDACTED]
- [REDACTED] Participants can be on stable dose of erythropoietin ( $\geq$  approximately 3 months);

- Absolute neutrophil count  $\geq 1.5 \times 10^9/\text{L}$ .

[REDACTED]

11. Subject has adequate renal function, defined as creatinine clearance  $\geq 60 \text{ mL/min}$ , as calculated using the modified Cockcroft Gault equation or other institutional standard formula, or creatinine  $\leq 1.5 \times$  upper limit of normal (ULN).

12. Subject has adequate liver function, defined as:

- Aspartate aminotransferase (AST) levels  $\leq 2.5 \times \text{ULN}$  (if liver metastases are present,  $\leq 5 \times \text{ULN}$ );
- Alanine aminotransferase (ALT) levels  $\leq 2.5 \times \text{ULN}$  (if liver metastases are present,  $\leq 5 \times \text{ULN}$ );
- Total bilirubin  $\leq 1.5 \times \text{ULN}$  (not applicable to subjects with Gilbert's syndrome).

- [REDACTED]

■ [REDACTED]

■ [REDACTED]

13. Subject has adequate coagulation function, defined as prothrombin time and activated partial thromboplastin time  $\leq 1.5 \times \text{ULN}$ , and International normalized ratio (INR)  $\leq 1.5$ . For subjects on anticoagulation therapy, the INR should be  $< 3.0$  or within the target range of anticoagulation therapy if applicable (INR should be used instead of prothrombin time for subjects on anticoagulation therapy).

14. [REDACTED]

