#### 6.7.1 Prohibited Concomitant Therapy (during treatment and within 28 days after drug discontinuation)

Patients should not receive other anti-tumor therapy while on treatment in this study, i.e. surgery, radiotherapy therapy, cytotoxic, biological, Chinese herbal medicine with anti-tumor indication, or hormonal other than replacement. Exception can be made for localized palliative radiotherapy for symptom control provided that the localized palliative radiotherapy does not compromise tumor assessments of target lesions. Other anti-tumor treatments should not be administered until

disease progression (as per clinical practice standards at the study center), unmanageable toxicity or no further clinical benefit occurs which requires permanent discontinuation of D-1553.

Patients are not allowed to take the following medications, except for management of AEs as advised by the Principal Investigator. Patients must stop taking these drugs for at least 14 days before dosing, except coumarin anticoagulants that can be stopped one week before inclusion (heparin of low molecular weight is acceptable):

- Any strong inhibitor and inducer of CYP3A4 used 2 weeks before inclusion and during the trial treatment phases (e.g. ketoconazole, clarithromycin, indinavir, itraconazole, etc. refer to [Appendix 4](#); however, this list may be not comprehensive, additional information may be obtained from the IFU of these drugs). In addition, herbals/supplements containing St. John's wart (*Hypericum perforatum* L.) and Seville orange etc. should also be avoided.
- [REDACTED]
- Any medications which can prolong QT interval or cause torsade de pointe (Refer to [Appendix 4](#)).

[REDACTED]

[REDACTED]

[REDACTED]

[REDACTED]

[REDACTED]

In the interest of patients' safety and acceptable standards of medical care, the Investigator will be permitted to prescribe the treatment(s) at his/her discretion.

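### Exclusion 13 lets subjects enter after a shorter washout of strong CYP3A4 and QT-prolonging drugs than section 6.7.1 demands, and the text on coumarin anticoagulants does not clearly agree either

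*Protocol*

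**What the plan says.** **Washout.** Protocol section 5.2, exclusion 13 (repeated in the synopsis), names several classes, among them "strong inducer or strong inhibitor of CYP3A4, with a known risk to prolong the QT interval or strong inhibitor of P-glycoprotein", and bars their use "within 14 days or 5 half-lives of the drug or its major active metabolite, whichever is shorter, prior to study day 1".

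Section 6.7.1 lists strong CYP3A4 inhibitors and inducers and QT-prolonging drugs as prohibited. Its lead-in says "Patients must stop taking these drugs for at least 14 days before dosing". The CYP3A4 bullet words the period a second way: "Any strong inhibitor and inducer of CYP3A4 used 2 weeks before inclusion and during the trial treatment phases".

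**Anticoagulants.** Section 5.1, inclusion 13 (also in the synopsis), accepts subjects on anticoagulation if the INR is below 3.0 or "within the target range of anticoagulation therapy if applicable", with INR replacing prothrombin time. Footnote 11 of Table 1-2 (Phase 1b) calls for coagulation tests "when clinically indicated or warfarin is to be administered". Section 6.7.1 qualifies its 14-day rule with "except coumarin anticoagulants that can be stopped one week before inclusion" and names low molecular weight heparin as acceptable.

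**Background.** Section 2.5 reports that phenotyping in human liver microsomes "identified CYP3A as the major metabolic enzyme" for D-1553.

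**The concern.** The opening of section 5 makes entry turn on the inclusion and exclusion criteria and forbids waivers. A site that applies exclusion 13 exactly may enrol a subject a day or two after the last dose of a short half-life interacting drug. The same subject then breaks a mandatory instruction in section 6.7.1. Two sites could decide differently on the same patient, and the deviation log would depend on which section the monitor reads.

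CYP3A is the main metabolic enzyme found for D-1553, so a recent strong inhibitor or inducer bears on early exposure. A recent QT-prolonging drug bears on the first on-treatment ECGs. Phase 1a escalates mostly on cohorts of three, judged on cycle 1, and the recommended Phase 2 dose is chosen from safety and PK data. Who enters those cohorts should not depend on which of two rules was applied.

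**Working it through.** The protocol has no figure of its own to reproduce here. The check is a comparison of text plus one break-even calculation.

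**1. Which classes overlap.** Strong CYP3A4 inhibitors and inducers, and drugs known to prolong QT, are visible in both passages. Exclusion 13 also names narrow-window CYP3A4 substrates and strong P-glycoprotein inhibitors. Part of the list in section 6.7.1 is redacted, so those two classes cannot be compared.

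**2. Where the durations part.** Exclusion 13 requires min(14 days, 5 × t½). Section 6.7.1 requires 14 days. They differ when 5 × t½ < 14 days, that is t½ < 14/5 = 2.8 days (67.2 hours), where t½ is that of the drug or its major active metabolite.

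**3. Size of the gap.** The documents give no half-lives for these drugs, so the first column is an assumption.

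| Assumed t½ | 5 × t½ | Exclusion 13 met after | Short of 14 days by |
|---|---|---|---|
| 6 h | 30 h | 1.25 days | 12.75 days |
| 12 h | 60 h | 2.5 days | 11.5 days |
| 24 h | 120 h | 5 days | 9 days |
| 48 h | 240 h | 10 days | 4 days |
| 67.2 h | 336 h | 14 days | 0 |

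**4. Reference points.** Study day 1 is the first dosing day, so exclusion 13 and the lead-in of section 6.7.1 count back from the same day. Only the CYP3A4 bullet and the coumarin clause, which count from inclusion, use another.

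**5. Which data are exposed.** A subject who stopped k days before Day 1 has been off the drug for k + 13 days at the nominal Day 14 visit. For k = 1.25, 2.5, 5 and 10 this gives 14.25, 15.5, 18 and 23 days, all at least 14. At the early edge of the visit window (4 days sooner) it gives 10.25, 11.5, 14 and 19 days. So the Cycle 1 Day 14 PK profile is little affected. The exposure is on Cycle 1 Day 1 PK and ECG (in Phase 1 and Phase 2) and in the early part of the cycle 1 DLT window.

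**6. Weight of one subject.** In a cohort of three, one such subject supplies 1/3 of the data; after expansion to six, 1/6. The documents give no basis for how many subjects would be affected.

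**7. Anticoagulants, side by side.**
- Inclusion 13 is an INR limit for subjects on anticoagulation, with a therapeutic target range as an alternative. It names no drug, but an INR target range fits coumarin-type therapy.
- Footnote 11 of Table 1-2 names warfarin as something that may be given in Phase 1b.
- Section 6.7.1 mentions coumarins in a timing exception. That shortens the lead time to one week but still reads as a requirement to stop.

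The three sit together only if inclusion 13 is read as covering other anticoagulants, or an INR taken before the coumarin is stopped, and footnote 11 as an exceptional use.

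**The case against.** The strongest reply on the washout is that both passages can be obeyed at once: 14 days off drug also satisfies exclusion 13. That is so, and the protocol does not give an impossible instruction. It does not settle the matter, because exclusion 13 expressly grants the shorter period and section 5 is what decides entry.

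Second, the effect may be small. After five half-lives (1/2)^5 = 1/32, about 3%, of the interacting drug remains, and section 6.7.1 bars further use during treatment. This stands as a limit on the size of the effect. A reader might go further and infer that a half-life rule is unsuitable for inducers because enzyme levels recover slowly; nothing in the documents addresses this, and it is not claimed here. A reader might also infer that the Day 14 profile is compromised; step 5 of the working shows that it largely is not. The CYP3A evidence quoted is in vitro, so it does not measure the share of clearance in patients.

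Third, the anticoagulant reading is an inference. Inclusion 13 names no drug, low molecular weight heparin is accepted, and INR may be measured during screening before a coumarin is stopped. The warfarin wording appears in the Phase 1b footnote, not in the visible Phase 1a or Arm B footnotes, and the Arm F counterpart is redacted. Section 6.7.1 also has an exception for managing adverse events and a closing sentence giving the investigator discretion to prescribe, whose scope is unclear after redacted text. A reader might conclude that a stable warfarin patient is flatly eligible under one section and barred by another, with a direct bleeding or thrombosis risk; the visible text does not establish either.

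Finally, text directly after exclusion 13 and within section 6.7.1 is blacked out and could contain an exception. That cannot be ruled out.

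**Conclusion.** For strong CYP3A4 inhibitors and inducers and QT-prolonging drugs, the visible protocol states two different entry washouts and does not say which governs. They differ for every drug with a half-life below 2.8 days, by 4 to 12.75 days over the assumed 6 to 48 hours. This part is a contradiction in operative text, subject only to the redactions. Its likely reach is Cycle 1 Day 1 PK and ECG and early cycle 1 safety, in cohorts small enough for one subject to matter; how often it would occur is unknown.

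The coumarin point is secondary: an unclear and probably inconsistent set of statements, not a proven contradiction. Nothing here judges which washout or which anticoagulant rule is clinically right.

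**What to change.** Reconcile exclusion 13, in section 5.2 and the synopsis, with section 6.7.1 so that one washout and one reference point apply to each class, and use the same reference point within section 6.7.1. Make inclusion 13, section 6.7.1 and footnote 11 of Table 1-2 say the same thing about coumarin anticoagulants. The sponsor chooses the rules.

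Optionally, use the concomitant medication records that section 6.7 already requires for the 28 days before first dose to flag subjects exposed within 14 days, and show Cycle 1 Day 1 PK with and without them.

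The cost is protocol wording. If the sponsor keeps the longer washout, some subjects who would pass exclusion 13 today start later, but section 6.7.1 as visible already asks that of them. The optional display needs no new data.

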### 5.3 Subject Completion and Withdrawal

#### 5.3.1 Subject Completion

In the dose escalation part of this study, a subject will be considered complete if he/she has a valid PK profile and has not withdrawn from the study prior to completing DLT observation period (at least one cycle). A subject will also be considered complete if he/she discontinued study treatment due to a DLT with or without a valid PK profile.

In other parts of the study, a subject is considered to have completed the study if he/she has completed study treatment as defined in the protocol, experienced disease progression, started another anticancer treatment, or been withdrawn by the investigator or sponsor for administrative reasons.

The end of the study for each subject is defined as the last visit of each subject. The end of the study is defined as the date of the last visit of the last subject in the study or last scheduled

procedure shown in the Schedule of Activities (SoA, Table 1-1 and Table 1-2 for Phase 1, Table 1-3 and Table 1-4 for Phase 2) for the last subject in the trial globally.

### **5.3.2 Subject Withdrawal**

A subject may withdraw from the study at any time at his/her own request or may be withdrawn at any time at the discretion of the investigator for safety, behavioral or administrative reasons. The subject will be definitively discontinued from both the study intervention and from the study at that time. If the subject withdraws from the study intervention, survival follow up may still be conducted until death, lost to follow-up or other reasons that a follow-up is not possible.

If the subject withdraws consent for disclosure of future information, the sponsor may retain and continue to use any data collected before such a withdrawal of consent.

If a subject withdraws from the study, he/she may request destruction of any samples taken and not tested, and the investigator must document this in the site study records.

At the time of discontinuing from the study, if possible, an early discontinuation visit should be conducted, as shown in the SoA (Table 1-1 and Table 1-2 for Phase 1, Table 1-3 and Table 1-4 for Phase 2).

Refer to the SoA (Table 1-1 and Table 1-2 for Phase 1, Table 1-3 and Table 1-4 for Phase 2) for data to be collected at the time of study discontinuation and follow-up and for any further evaluations that need to be completed.

